## Abstract

**Abstract:**

**Introduction:**

Neurodevelopmental impairments in congenital heart disease (CHD) are the most frequent long-term morbidity. Adverse neurodevelopmental outcomes may start in the prenatal period. Maternal mental health may be a potentially modifiable risk factor for the optimisation of neurodevelopment in CHD. We propose to assess the impact of prenatal maternal mental health on 1-year neurodevelopmental outcomes in complex CHD.

**Methods and analysis:**

Neuro-Moms CHD is a national multi-centre, prospective study of prenatal maternal mental health and neurodevelopmental outcomes in children with complex CHD who undergo neonatal open-heart surgery. Participants (n=87 mother-child dyads) will be recruited from five major French paediatric cardiology centres (Necker Children’s Hospital in Paris, Bordeaux Cardiology Hospital, Marseille Children’s Hospital, Montpellier University Hospital and Saint-Pierre Institute). Expecting women who receive a prenatal diagnosis of fetal complex cyanotic CHD that requires a neonatal open-heart surgery for the newborn are eligible to participate. They will complete self-reports on mental health, anxiety, depression and coping skills and will participate in a semi-structured psychological interview. Mothers will provide information on medical, sociodemographic and lifestyle factors. They will be enrolled during the third trimester of pregnancy and will participate at three time points: prenatal, T1; after the newborn’s cardiac surgery, T2; and between 12 and 18 months after birth of the child with CHD, T3. Children with CHD will undergo a standardised neurodevelopmental assessment when they turn 12–18 months old. The father or co-parent of the child with CHD will also participate in T1 and will complete mental health self-reports. We will use a structural equation model to estimate simultaneously the relationships among maternal mental health, prenatal factors and child neurodevelopment outcomes.

**Ethics and dissemination:**

This study is sponsored by the French National Institute of Health and Medical Research. It was approved by the Ethics Committee on 5 November 2024 and is registered in a public trials registry (NCT06711666). Neuro-Moms CHD targets a public health question with important societal implications. Results are expected to be broadly communicated with the scientific community and the lay public. Dissemination of findings will be in the form of scientific articles in peer-reviewed journals and presentations at conferences. Any publication or communication will comply with the international recommendations: ‘Recommendations for the Conduct, Reporting, Editing, and Publication of Scholarly work in Medical Journals’ (http://www.icmje.org/recommendations). All participants will give written informed consent or assent to participate. The anonymised data to be collected in this study will be available within the manuscripts published.

**Trial registration number:**

NCT06711666; pre-results.

STRENGTHS AND LIMITATIONS OF THIS STUDYThis is a national, multi-centre study, which will help to improve the care pathway for children with congenital heart disease (CHD).In addition to the assessment of mental health in the prenatal period using standardised self-report questionnaires, a 45 min semi-directive interview will be conducted by a psychologist with expertise in perinatal mental health, enabling a more detailed assessment of the complexity of mental health in the prenatal period in expecting mothers with a CHD diagnosis.This study is longitudinal and will provide a neurodevelopmental assessment at age 1 for children with CHD, but neurodevelopment is a long trajectory: children’s cognitive, behavioural and socio-emotional development should be evaluated again at different ages and stages of their life.

## INTRODUCTION

 Congenital heart disease (CHD) represents 1% of live births and is the leading cause of congenital malformations at birth.^1 2^ Advances in cardiac surgery and medical management of CHD have increased the survival and life expectancy of children with the most complex forms of CHD through interventions performed during the neonatal period. This increase in the population living with cyanotic CHD has been accompanied by an increased recognition of their long-term morbidities. North American guidelines from the American Heart Association consistently highlight the fact that neurodevelopmental outcomes in CHD are a pressing public health issue.^3 4^

Neurodevelopmental impairment in children born with CHD has a multifactorial aetiology, with a probable synergy between risk factors that has yet to be elucidated.^5^ Many factors interact and/or accumulate which contribute to these long-term morbidities. It has been established that the origins of neurodevelopmental impairments may start in the prenatal period,^6^ or even at conception, with some genetic overlap between CHD and neurodevelopmental disorders.^7^ Pathophysiological mechanisms, already observed in the prenatal period, suggest that certain CHD described as cyanotic, like Transposition of the Great Arteries (TGA) or Hypoplastic Left Heart Syndrome, can influence early brain development by inducing hypoxia and/or cerebral hypoperfusion.^8 9^ As a result, the fetal brain develops in conditions of insufficient oxygen supply, leading to a dysmature brain with lesions detectable as early as the second trimester of pregnancy.^10^

The neonatal period is also crucial for children with complex CHD, marked by insults on the developing brain, such as frequent episodes of hypoxia and heart failure, which can aggravate damage to an already vulnerable brain. Postnatal diagnosis of critical CHD,^11 12^ neonatal interventions, including cardiac surgery and selective cerebral perfusion,^13^ are also factors considered in the onset of neurodevelopmental impairments. To date, distinguishing causal factors from intermediate or confounding factors remains a complex task. Initially, cardiac surgery and related surgical and medical factors were thought to be among the major risks implicated with neurodevelopmental disorders in CHD.^14^ However, despite advances in surgical techniques and management, these disorders persist, suggesting that the variance attributable to the medical management of CHD may not be dominant. Importantly, lifestyle factors, such as the child’s living environment and socioeconomic factors (economic status, accessibility to care, parental education),^15^ also appear to influence these impairments.

It is increasingly recognised that prenatal risk factors play a prominent role in the neurodevelopmental prognosis for children with critical CHD. Recent data obtained from a cohort of pregnant women whose fetus was diagnosed with complex CHD showed that cerebral growth delay (ie, reduced cortical volumes) was observable in utero, and that this delay was predictive of poorer cognitive and motor prognosis at age 2.^16^

Some prenatal factors have been recognised as playing a crucial role in the emergence and severity of neurodevelopmental impairments in children with CHD.^12 17 18^ Our previous study evaluated the impact of prenatal diagnosis of one of the most studied complex cardiac malformations, TGA, on neurocognitive outcomes. Findings from this study showed that a prenatal diagnosis of TGA was associated with better neurocognitive scores, particularly in executive functions, in preschool and school-aged children.^12^ In addition, findings from the largest French population-based cohort, Epidemiology of Congenital Heart Defects (EPICARD), demonstrated that perinatal factors associated with in-utero developmental delay, such as low birth weight for gestational age, were deleterious to neurodevelopmental prognosis in CHD.^19^ In utero developmental delay has been linked to poor maternal mental health in the general population.^20^ It is unknown whether prenatal maternal psychological distress has an impact on neurodevelopmental outcomes in children with CHD.

### Maternal mental health disorders and neurodevelopmental outcomes

Maternal mental health disorders are a significant concern in public health. Pregnancy and the post-partum period, which are particularly vulnerable in terms of biological and psychological changes, significantly increase the risk of developing a mental health disorder. Impaired maternal mental health is now recognised as one of the main peripartum and post-partum morbidities, with postpartum depression affecting up to 22% of women during the prenatal period or the first post-partum year.^20^ This percentage rises in the case of complicated or high-risk pregnancies, particularly when the fetus is diagnosed with CHD.^21^,^23^ These expecting women are faced with a multitude of sources of stress, ranging from invasive complementary examinations (eg, amniocentesis) to prognostic uncertainty about the health of the unborn child. In this context, the risk of maternal mental health deterioration dramatically rises, with a particularly high incidence of depressive states, anxiety disorders and post-traumatic stress disorder (PTSD) in the perinatal period.

In the absence of a specific fetal diagnosis, maternal mental health may be linked to changes in fetal brain development in utero, as well as to potential long-term cognitive, emotional and behavioural impairment in the child.^24^,^27^ Thus, maternal mental health appears to influence the neurodevelopment of the unborn child by modulating, in utero, both cerebral maturation and postnatal psychological attachment processes.^27^ More specifically, a recent study showed that perinatal maternal depression was related to the complexity or severity of the unborn child’s CHD, and that maternal stress and anxiety were associated with smaller cerebellar and hippocampal volumes in the fetus.^28^

Maternal psychological distress may be a potentially modifiable risk factor in the optimisation of neurodevelopment in CHD. However, to date, no study has investigated the link between prenatal mental health and neurodevelopmental outcomes in children with CHD. Similarly, although studies have emphasised the importance of maternal psychological support following fetal diagnosis of CHD, very few studies have focused on understanding the determinants of maternal mental health and their potential direct or indirect impact on the neurodevelopment of children with CHD. A better understanding of these psychological, medical and sociodemographic determinants, linked to the mother and linked to the child with CHD, is essential for risk stratification in terms of both maternal mental health and the neurodevelopmental outcome of children with CHD. Understanding the impact of psychological factors on neurodevelopmental impairments in children with CHD is crucial for designing preventive interventions that enhance neurodevelopment. Neuro-Moms CHD is the first multicentre longitudinal study to focus on the impact of prenatal maternal mental health on 1-year neurodevelopmental outcomes in children with complex cyanotic CHD who undergo neonatal open-heart surgery (ie, children at high neurodevelopmental risk).

### Aims and hypotheses

#### Main objective

*Aim 1*: To characterise the impact of prenatal maternal psychological distress on neurodevelopmental outcomes at age 1 for children with cyanotic CHD who undergo neonatal open-heart surgery. We hypothesise that a higher level of maternal psychological distress as measured by the Symptom Check-List-90 R (SCL-90-R)^29^ will be associated with lower standardised neurodevelopmental scores as measured using the Bayley Scales of Infant and Young Child Development, Fourth edition (Bayley-4^30^) in children with CHD.

#### Secondary objectives

*Aim 2*: To describe the evolution of maternal mental health (ie, anxiety, depression and psychological adjustment scores), from the antenatal period to the neonatal postoperative period (after cardiac surgery), and finally when the child with CHD turns 1 year. We predict that maternal psychological distress will decrease over time, as we expect that the most acute period of stress will be closest to the initial diagnosis of fetal CHD (T1, T2 and T3).

*Aim 3*: To identify the medical and sociodemographic factors associated with prenatal maternal psychological distress of women carrying a fetus diagnosed with cyanotic CHD. We hypothesise that lower maternal educational attainment and poor family support as well as fetal factors such as diagnosis of severe CHD (ie, univentricular heart) will be associated with worse prenatal maternal mental health outcomes (ie, overall mental health, anxiety and depression symptoms). The evaluation of scores obtained on self-report questionnaires (SCL-90-R,^29^ State-Trait Anxiety Inventory (STAI-Y),^31^ Coping Inventory for Stressful Situations (CISS),^32^ Edinburgh Postnatal Depression Scale (EPDS),^33 34^ Posttraumatic Stress Disorder Checklist for DSM-5 (PCL-5)^35 36^) completed by the mother will be analysed in relation to medical, sociodemographic and lifestyle factors.

*Aim 4*: To explore the mediating role of prenatal risk factors (ie, medical factors and maternal coping strategies, such as task-oriented, avoidant and emotional coping) in the association of prenatal maternal mental health (ie, distress, anxiety and depression) and neurodevelopment in children with CHD. We will also explore the potential interaction effects between sociodemographic factors and mental health on neurodevelopment in CHD. We hypothesise that expecting mothers with low socioeconomic levels of support and/or with maladaptive coping strategies (eg, avoidant, emotional reactivity) will experience the greatest effects of prenatal distress on their children’s neurodevelopmental outcomes at 1 year of age. The mediating role of medical and psychological antenatal factors (information extracted from the medical record, the interview and the information questionnaire) on the relationship between maternal mental health scores (SCL-90-R, STAI-Y, CISS, EDPS, PCL-5) and the child’s neurodevelopment (Bayley-4,^30^ Ages and Stages Questionnaire-Third Edition (ASQ-3)^37^) will be characterised.

*Exploratory Aim 5*: To explore the impact of the mental health of the father or co-parent of the child diagnosed prenatally with CHD on the cognitive neurodevelopment score of the child at age 1. The SCL-90-R (general mental health), STAI-Y (anxiety symptoms) and CISS (coping skills) self-report questionnaires will be presented to the co-parent only in Time 1 (concomitantly with the maternal prenatal questionnaires). The Global Score Index of the SCL-90-R will be used as an indicator of the co-parent’s mental health.

## METHODS AND ANALYSIS

### Study design

This is a national multicentre, non-interventional, prospective and longitudinal study of prenatal maternal mental health and child’s neurodevelopmental outcomes in CHD (n=87 mother-child dyads). Expecting women who consent to participate will undergo psychological evaluations. These evaluations will be conducted by a psychologist with expertise in perinatal mental health. This psychological assessment is conducted at three time points:

Time 1 (T1), during the third trimester of pregnancy (prenatal period), between 28 and 38 weeks of gestation;Time 2 (T2), after the child’s cardiac surgery, and before their hospital discharge (ie, in the postnatal period, after intensive care transfer to inpatient care); andTime 3 (T3), between 12 and 18 months after birth of the child with CHD.

The father or co-parent of the unborn child will also be invited to participate in the study at Time 1 by completing self-report questionnaires similar to those of the expecting participant. The child with CHD will be involved in a neurodevelopmental assessment when he/she is 12–18 months of age. This visit will be integrated into his/her usual cardiac neurodevelopmental care, whenever possible.

### Participants and recruitment

Participants are (1) expecting women carrying a fetus prenatally diagnosed with an isolated cyanotic CHD that is not associated with known genetic syndromes and/or major extra-cardiac anomalies; (2) their child with CHD when they turn age 12 months (+6 months maximum) at the time of the neurodevelopmental examination (T3); and the father or co-parent of the child (invited to participate during the prenatal period only). Expecting women are included if they meet the following criteria: (1) expecting woman aged ≥18 years old who received a prenatal diagnosis of isolated fetal complex cyanotic CHD confirmed by a paediatric cardiologist; (2) pregnancy at week 28 minimum (third trimester) and up to week 38 of gestation maximum; (3) a delay of 4 weeks minimum between initial fetal diagnosis of CHD and study participation; (4) women living in France and being followed-up at one of the participating cardiology centres and (5) social security in France or Europe. Children with CHD are included if they meet the following criteria: (1) received a prenatal diagnosis of isolated fetal complex CHD and child of a woman included in the study; (2) consent of both parents or legal guardians; (3) social security in France or Europe. Co-parents are included in the study if they meet the following criteria: (1) co-parent aged ≥18 years old with an expecting woman already included in the study; (2) social security affiliation in France or Europe. Only participants who were able to understand the questionnaires independently or via a direct translation, if needed (ie, only those who spoke French or English) were included in this study.

Exclusion criteria will be, for expecting women and co-parents: (1) refusal to participate; (2) fetus with CHD associated with other fetal comorbidity that has a clinical impact on neurodevelopment (ie, genetic syndromes such as trisomy 13-18-21, poly-malformative syndromes, cerebral malformations) or according to the clinical judgement of the investigator; (3) wish for medical termination of pregnancy at the time of inclusion; (4) inability to understand and/or complete the self-report questionnaires; (5) medical diagnosis of severe psychiatric disorder (eg, psychotic disorders, major depressive disorders), with or without treatment (a referral for perinatal psychiatric consultation will be proposed to patients excluded due to these conditions); (6) under court protection, guardianship or conservatorship. Exclusion criteria will be, for children: (1) genetic abnormality, cerebral malformation making it impossible to evaluate the child using the standard neurodevelopmental tools chosen for the study.

Participants will be recruited from the two French M3C (complex congenital heart defects) reference centres, Hôpital Necker Enfants Malades and CHU de Bordeaux, as well as the centres of competence for complex congenital heart defects, CHU de Montpellier, AP/HM Hôpitaux de Marseille and Institut Saint Pierre, during a fetal cardiology follow-up consultation. The Principal Investigator (PI) of the study (JC) delegates local PIs in each centre to ensure multi-site coordination. The local PIs will ensure local regulatory compliance.

Information and inclusion of participants will be carried out by the fetal cardiologists who provide antenatal consultations in congenital cardiology, or by a qualified investigator (neuropsychologist or clinical psychologist). The study will be proposed at least 4 weeks after the initial diagnosis of CHD, to provide appropriate time for the family to process and decide on the continuation of pregnancy.

### Patient and public involvement

The research questions and outcomes of this study were developed by considering mental health challenges in the context of a prenatal diagnosis of CHD, and aiming for the optimal development of the child, which is a priority for every parent. Patient association ‘Petit Coeur de Beurre’ was involved in the identification of key mental health questions for this study. They will be involved in the dissemination of results to parents of children with CHD.

### Primary outcome measures

The primary outcome will be the relationship between the global mental health self-report questionnaire (SCL-90-R) at the prenatal evaluation (T1)^29^ and neurodevelopmental outcomes at age 1 measured via the Bayley-4.^30^ The SCL-90-R is a 90-item self-administered questionnaire assessing the psychological distress and mental health profile of adults. Each item is rated on a five-point Likert scale, from 0 (= not at all) to 4 (= extremely), according to the distress caused by each symptom. It assesses nine primary symptom dimensions: somatisation, obsessive-compulsive, interpersonal sensitivity, depression, anxiety, hostility, phobic anxiety, paranoid ideation and psychoticism. Three global indices provide measures of overall psychological distress: the global severity index (GSI), the positive symptom total and the positive symptom distress index (PSDI). The internal consistency of the SCL-90-R is satisfactory (α=0.54 to 0.84 for the French validation in adults).^28^ The GSI will be retained as the primary indicator of mental health in this study because it is the most sensitive indicator of the subject’s psychological distress, combining information on the number of symptoms and the intensity of psychological distress. The GSI is a standardised T-score (mean 50, SD 10).The cognitive score of Bayley-4^30^ will be used as the primary indicator of neurodevelopment in children with CHD at age 1 in this study. The Bayley-4 is a multidomain assessment tool of development in children, supporting early detection of developmental issues by measuring five key domains: cognitive, language, gross and fine motor and social-emotional. Bayley-4 scores are standardised and reported as standard scores (mean 100, SD 15). The Bayley-4 is the most widely used cognitive tests between the ages of 18 and 40 months^38^ and has solid psychometric qualities.^39 40^

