#### Secondary objectives

##### Aims 2 and 3

In order to study changes over time (ie, evolution of maternal mental health) in the scores obtained on the self-report questionnaires (SCL-90-R, STAI-Y, CISS, PCL-5, EPDS) completed by the mother and to study changes as a function of medical, sociodemographic and lifestyle factors, a linear mixed model will be applied. This model takes into account the random effect induced by the analysis of three repeated measurements. The cofactors tested (fixed effects) will be the variables likely to influence the scores on these self-report questionnaires (medical, sociodemographic and lifestyle). The results of the linear mixed model are expressed for each factor in the form of a coefficient corresponding to the variation brought about by this factor on the basal score (intercept). A positive coefficient indicates a score-raising effect, while a negative coefficient indicates a score-lowering effect. For the time effect, the coefficient reflects the variation during the follow-up, while for the other factors, the estimate reflects the variation induced by the presence of the factor. The interactions between the co-factors and time will also be tested. A similar methodology will be applied for each score.

##### Aim 4

We will use a structural equation model to estimate simultaneously the relationships among maternal mental health (as captured by SCL-90-R, STAI-Y, CISS, PCL-5 and EPDS scores), prenatal factors (medical, sociodemographic and psychological) and child development (Bayley-4 and ASQ-3).

The structural pathways linking these three latent constructs, whereby maternal mental health impacts prenatal factors, which in turn influence the child’s development, while also allowing for a residual direct effect of maternal mental health on developmental outcomes.

We will quantify the mediating role of each block of prenatal factors by estimating the proportion of the effect of maternal mental health on child development that is transmitted through those factors. The model will be fitted using robust maximum likelihood estimation, with bootstrapping to derive CIs for indirect effects.

##### Aim 5

The GSI of the SCL-90-R will be used as an indicator of co-parent mental health. It is a standardised score with a T-score (mean 50, SD 10). The Bayley-4 cognitive score will be used as an indicator of neurodevelopment in children with CHD at age 1. This is an exploratory analysis, independent of the primary outcome.

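### In the SCL-90-R part of Aim 2, the GSI change from late pregnancy (T1) to 12–18 months after birth (T3) cannot be separated from the resolution of bodily pregnancy symptoms, because the index includes somatisation

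*Protocol article*

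**What the plan says.** Under Primary outcome measures, the article describes the instrument: "The SCL-90-R is a 90-item self-administered questionnaire", with items "rated on a five-point Likert scale, from 0 (= not at all) to 4 (= extremely), according to the distress caused by each symptom". On content it states: "It assesses nine primary symptom dimensions: somatisation, obsessive-compulsive, interpersonal sensitivity, depression, anxiety, hostility, phobic anxiety, paranoid ideation and psychoticism". It then fixes the summary score: "The GSI will be retained as the primary indicator of mental health in this study", on the ground that it is sensitive and works by "combining information on the number of symptoms and the intensity of psychological distress". No dimension is said to be left out of the index.

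On timing, Study design places T1 "during the third trimester of pregnancy (prenatal period), between 28 and 38 weeks of gestation" and T3 at 12 to 18 months after birth. The Procedures text gives the SCL-90-R at T1 and T3 but not at T2, where only the EPDS, STAI-Y and CISS are listed.

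On the hypothesis, Aim 2 states: "We predict that maternal psychological distress will decrease over time". The reason offered is that stress is most acute nearest the fetal diagnosis. No size of decrease is set. On the analysis, the Data analysis plan for Aims 2 and 3 applies a linear mixed model to each questionnaire score, the SCL-90-R included, and explains: "For the time effect, the coefficient reflects the variation during the follow-up".

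**The concern.** The GSI is a global index over all nine dimensions, and one of them is bodily complaints. If such complaints are raised in late pregnancy for physical reasons and have largely gone a year or more after birth, the GSI falls between T1 and T3 even if nothing psychological has changed. That physical premise is general clinical knowledge and is not stated in the documents.

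The design offers no way to separate the two explanations for this scale. Every woman is pregnant at T1, T3 is at least 12 months after birth, and no pregnant comparison group is described. Pregnancy status and time therefore coincide, and none of the factors listed under Covariate measures can pull them apart in the mixed model. Because the prediction has a direction but no size, any significant fall in the GSI would count as support.

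At stake is one statement in the results: that overall distress fell as the diagnosis receded. The stated rationale is psychological, and the time coefficient for the GSI cannot by itself support it.

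**Working it through.** **Plan's own figure.** The documents give no figure for the T1–T3 change in GSI. The only sample size stated, 72 evaluable and 87 included dyads, belongs to the main objective. The 72 reproduces as a 10-df test of an R² increase of 0.20 over a base R² of about 0.20, with 90% power and alpha 5%; the 87 is 72 × 1.2 = 86.4, rounded up. These figures serve here only to suggest how many pairs Aim 2 might have: 87 × 0.8 = 69.6, about 70.

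**Which scales can show change at all** (from the Procedures text; the schedule figures are not shown):

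| Scale | T1 | T2 | T3 |
|---|---|---|---|
| SCL-90-R | yes | no | yes |
| STAI-Y | yes | yes | yes |
| CISS (coping) | yes | yes | yes |
| EPDS | no | yes | no |
| PCL-5 | no | no | yes |

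Only the SCL-90-R and STAI-Y can trace distress over time. Depression is measured more than once only through the SCL-90-R depression dimension.

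**Inputs from the documents:** 90 items; T-score SD 10; about 70 pairs.

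**Assumed inputs, not in the documents:** 10–12 somatisation items; a mean fall of 0.25–1.0 point per somatic item on the 0–4 scale, all other items unchanged; raw GSI SD 0.35–0.50, taken as equal to 10 T-points; T1–T3 correlation 0.6.

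**Formulas**

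- Artefactual raw fall = items × fall per item / 90.
- In SD units: e = raw fall / raw SD. In T-points: 10 × e.
- SD of the change in SD units: √(2 × (1 − 0.6)) = 0.894. Standard error: 0.894/√70 = 0.107.
- Smallest significant fall: 1.96 × 0.107 × 10 ≈ 2.1 T-points.
- Chance of a significant fall (two-sided 5%, normal approximation): Φ(e/0.107 − 1.96).

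**Results**

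| Fall per item | Low case: 10 items, SD 0.50 | High case: 12 items, SD 0.35 |
|---|---|---|
| 0.25 | 0.028 raw, 0.6 T, z 0.52, 7% | 0.033 raw, 1.0 T, z 0.89, 14% |
| 0.50 | 0.056 raw, 1.1 T, z 1.04, 18% | 0.067 raw, 1.9 T, z 1.78, 43% |
| 1.00 | 0.111 raw, 2.2 T, z 2.08, 55% | 0.133 raw, 3.8 T, z 3.56, 95% |

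With no shift, the chance of a significant result in this direction would be 2.5%.

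**Sensitivity.** With 72 pairs, raw SD 0.3–0.5 and correlation 0.5–0.7, the chances are about 7–23% (0.25 point), 15–68% (0.5 point) and 47% to over 99% (1.0 point).

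**The case against.** Several arguments on the other side have force.

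- **The GSI is not the whole of Aim 2.** The aim speaks of anxiety, depression and adjustment scores, and the mixed model is run for each questionnaire. The STAI-Y is measured at all three times, so a GSI fall beside flat anxiety scores would be visible. A reader might infer that the whole Aim 2 prediction could be confirmed by somatic symptoms alone; the documents do not support that. What remains is that the STAI-Y checks anxiety only, and that neither the EPDS nor the PCL-5 is repeated.
- **Aim 1.** A reader might also infer that the primary regression is biased through obstetric complications. The article collects gestational age, gestational diabetes, hypertension and placental abnormalities, and adjusts the primary model for medical factors. That largely addresses such a link. What is left is noise from ordinary pregnancy symptoms, and its size in Aim 1 has not been estimated.
- **The magnitude is assumed.** Item count, item change, raw SD and correlation all lie outside the documents. The range is wide, and its top needs the most unfavourable values of item count, fall and SD together. Items are also rated by the distress a symptom causes, so expected pregnancy symptoms need not score high. This stands: the calculation shows that the artefact is possible, not that it is likely.
- **Norms.** The article describes its French validation only as being in adults. Whether pregnant women were in that sample cannot be seen, so nothing is built on it here.
- **Left to the analysis plan.** The Aim 2 plan names SCL-90-R scores and does not rule out reporting by dimension; a separate plan may add it. However, the article itself fixes the index, the two time points, the direction of the prediction and the reading of the time coefficient. The point concerns that combination, not an absent detail.

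**Conclusion.** The point holds for the SCL-90-R part of Aim 2, a secondary aim. As planned, the GSI time effect is inseparable from the end of pregnancy, and the somatisation items would move it in the predicted direction. That structural conclusion follows from the article's own choices, together with the outside premise that bodily complaints are higher in late pregnancy than a year or more after birth.

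The size is not known. Under the stated assumptions, the GSI would drop by about 0.6 to 3.8 T-points with no other change, against a significance threshold of about 2.1, and the chance of a significant fall from this alone is about 7% to 95%. At the low end the effect is small; from about half a point per item upward it could mislead. The STAI-Y limits the damage for anxiety but not for overall distress or depression. This is an inexpensive improvement to make before the data are seen. It does not undermine the primary objective.

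**What to change.** Keep the GSI as the primary index. For the Aim 2 change from T1 to T3, prespecify that the SCL-90-R is also reported as (a) the mean of the non-somatisation items and (b) the depression and anxiety dimension scores. State that a fall in the GSI will be interpreted alongside these and the STAI-Y, and will not be attributed to reduced psychological distress if it is confined to somatisation. This is a rule of interpretation: the recomputed index should not hold a formal veto, since somatisation belongs to the instrument's own construct.

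Repeating the Aim 1 regression with the non-somatisation index is an optional sensitivity analysis, because adjustment for medical factors is already provided for.

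The cost is rescoring item responses already collected and a few extra mixed-model fits, with no new visit or questionnaire. The downside is that the recomputed index has no published T-score and must be analysed as a raw mean, so its change cannot be read on the T-scale used for the GSI.
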